### Measures

Demographics items include both standard demographics as well as items to assess gender identification and sexual orientation. Items to assess general medical history and history of pelvic floor disorders are included. The survey packet also includes items to assess current LUTS and validated measures that serve as external criterion in establishing external validity. Details of the criterion instruments are further described below (Table 4). Dependent on branching, the number of items a respondent is presented ranges from 63 to 90 items. The total PAPI survey length, inclusive of all self-report measures, is 49 pages.

**Table 4 Tab4:** External criterion measures for validation assessment

Measure	Data source	Data method	Validation type
*Same source, same method (self-reported measures)*			
PLUS-BHI	Self	Survey	–
MOS-SF 36*	Self	Survey	Convergent
KHQ	Self	Survey	Convergent
UDI-6	Self	Survey	Convergent
POPDI	Self	Survey	Divergent
CRADI	Self	Survey	Divergent
BFLUTS	Self	Survey	Convergent
*Same source, different method*			
Bladder diaries: 1-day 2-day	Self	Activity log	Convergent
*Different source, different method*			
Judge BH rating: Aided Unaided	Other/expert	Qualitative	Convergent Divergent
*Different independent source, different method (objective measures)*			
PTT	Other/technical	Volume calculation	Convergent Divergent
Uroflowmetry	Voiding dynamics	Rate calculation	Convergent Divergent
PVR volume	Imaging	Volume calculation	Convergent Divergent
Urinalysis	Dipstick/biologic	Standardized lab Analysis	Convergent Divergent

^*****^Ten selected items from the Medical Outcome Study Short Form Health Survey (MOS SF-36)

KHQ, King’s Health Questionnaire; UDI, Urogenital Distress Inventory; BFLUTS, Bristol Female Lower Urinary Tract; PFDI-20, Pelvic Floor Distress Inventory; CRADI, colorectal and anal distress inventory; POPDI, pelvic organ prolapse distress inventory; PPT, Paper Towel Test for stress incontinence; PVR, post-void residual volume measurement by bladder scan

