### Analysis plan

Item distributions will be evaluated for floor and ceiling effects. Items that exhibit greater than 85% response in the tail of the distribution will be removed. Item non-response will be evaluated with items demonstrating greater than 20% non-response considered for removal. Test–retest reliability will be evaluated for all items comparing item response on initial PLUS-BHI completion to item response on retest version of PLUS-BHI using Bland–Altman with 95% interval agreement threshold will be used for comparison of continuous variables (including categorical variables with greater than 6-point response options), and chi-square used for comparison of categorical variables, with Fisher’s exact used as needed.

A comparison of responses by mode (PAPI vs. CASI) will be made both between and within responses from the general population sample and the clinical samples separately. Items will be evaluated using Tukey’s HSD or chi-square (Fishers as needed). Items demonstrating significant differences across mode of administration or across sample will be considered for removal.

Internal dimensional validity will be identified and evaluated using factor analytic approaches. Two investigators utilizing multiple methods principal component analysis and factor analysis and rotation methods (orthogonal/oblique) will work independently and periodically compare and discuss results. Internal consistency of item groupings will be evaluated with Cronbach’s alpha. Item groupings with alpha > 0.9 will be further evaluated to determine whether items within grouping are, in reality, subtle variations of the same question. Item groupings with alpha < 0.4 will be rejected. Several criteria will be applied in evaluation of dimensions and factor retention: the Kaiser-Guttman rule (Eigenvalues > 1.0), factor loading thresholds of 0.60/0.40, scree plots, Kaiser–Meyer–Olkin (KMO) residuals off-diagonal partial correlations measure of sampling adequacy > 0.70 [28, 39, 40]. This analysis will be iterative. Emergent factor structures across mode and sample will be compared with the aim of identifying factor structures that are consistent across mode and across sample. The postpartum sample data will be evaluated similarly, with comparison of the factor structure made to final factor structure from general population sample and general clinical sample.

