Our evaluation of levels of evidence is based on the work of Campbell and Fiske’s Multitrait-Multimethod (MTMM) matrix relative to the use of multiple-operationalism (multiple items to assess the range of a concept) to evaluate and establish levels of validity, although we use the term “dimension” in lieu of “trait.” [31]. Correlation values across multiple data sources and methods within each emergent dimension (factor) populating the MTMM matrix will allow evaluation of convergent validity and divergent validity.

Sample sizes are based on ensuring sufficient numbers of item response to conduct factor analysis. We aim to enroll the number of women necessary to achieve 10 participants per PLUS-BHI item included in the dimensional analysis [41], although less conservative estimates of 5–10 participants per item have been suggested [42]. Based on a maximum of 90 items a participant may respond to, our target number of completed BHIs in the general population sample (n = 694) and the clinical sample (n = 354) provides 8 and up to 12 participants per item evaluated, dependent on merging samples. This estimate is also conservative in that it accounts for all branching and not all participants will indeed branch based on their responses.

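### Eigenvalue > 1 is the only numeric rule for the number of factors, and with up to 90 items it over-extracts; with skewed items this can split true dimensions in the clinical sample

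*Protocol article*

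**What the plan says.** The Analysis plan names several criteria for judging dimensions and keeping factors. They include "the Kaiser-Guttman rule (Eigenvalues > 1.0), factor loading thresholds of 0.60/0.40, scree plots" and a KMO "measure of sampling adequacy > 0.70". For reliability it says "Item groupings with alpha < 0.4 will be rejected", and groupings with alpha above 0.9 are checked for redundancy. Two investigators work independently with several extraction and rotation methods. The work is iterative and looks for structures that agree across mode and sample. Before that, items with more than 85% of responses in the tail are removed.

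The sample size is argued from participants per item. The plan takes 90 as the largest item count after branching and sets a target of 694 for the general population. On the resulting ratio it says "the clinical sample (n = 354) provides 8 and up to 12 participants per item evaluated, dependent on merging samples". The Measures section adds that "the number of items a respondent is presented ranges from 63 to 90 items".

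**The concern.** Of the listed criteria, only eigenvalue > 1 produces a number of factors. A scree plot is read by eye, loading thresholds assign items to factors already extracted, and KMO judges whether the correlation matrix as a whole suits factoring. With many items, sampling error alone lifts a large share of eigenvalues above 1. If too many factors are then rotated, one real dimension can break into several small groupings, and an alpha floor of 0.4 is low enough to let such fragments stand.

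The emergent dimensions feed the multitrait-multimethod matrix. A dimension of low reliability weakens its convergent correlations and can make divergence look better than it is. The number of components above 1 also changes with N, so part of any difference in structure between samples or modes could come from sample size alone.

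**Working it through.** **The plan's own figure.** 694/90 = 7.7, rounded to 8. (694 + 354)/90 = 1048/90 = 11.6, rounded to 12. The stated participants per item are reproduced.

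**Inputs from the protocol article.** 63 to 90 items; N = 694 (general), 354 (clinical), 1048 (merged) and 154 (postpartum). Clinical mode is allocated 1:2, so 354 × 2/3 = 236 CASI and 354 × 1/3 = 118 PAPI. Thresholds: eigenvalue 1, loadings 0.60/0.40, KMO 0.70, alpha 0.4.

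**Method.** Simulation: principal components, keep eigenvalues > 1, varimax rotation, form groups of at least two items at the loading threshold, compute alpha. The comparator is parallel analysis (95th percentile of random data with the same N and number of items).

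**1. Pure noise, normal items, 100 runs per setting**

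| N | Components > 1 (90 items) | Runs with any group at alpha ≥ 0.4 (loading 0.40; 63 and 90 items) | Mean KMO |
|---|---|---|---|
| 1048 | 42.2 | 0% and 0% | 0.48-0.49 |
| 694 | 41.6 | 0% and 0% | 0.47-0.48 |
| 354 | 40.1 | 0% and 1% | 0.43-0.45 |
| 236 | 39.1 | 17% and 35% | 0.38-0.43 |
| 154 | 37.6 | 91% and 98% | 0.30-0.38 |
| 118 | 36.5 | 100% and 100% | 0.20-0.32 |

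With 63 items the count above 1 is about 29 to 30 at N = 354 to 1048. Parallel analysis keeps essentially none.

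**2. Five true factors, normal items** (assumed: 18 items each, loading 0.6, factor correlation 0.4). Eigenvalue > 1 keeps about 11 at N = 694 and 18 at N = 354; other runs gave 13 and 19. After loading 0.40 and alpha 0.4, 5.00 groups remain at N = 694 and 5.04 at N = 354. Parallel analysis keeps 5.

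**3. Five true factors, skewed ordinal items** (assumed: five categories, 40-80% at the floor, which the 85% tail rule allows; factor correlation 0.4; 25 runs; loading 0.40 and alpha 0.4):
- N = 354, mean loading 0.5: 30.8 components above 1; 8.5 groups pass, 6.2 of them with alpha 0.4-0.7; KMO 0.76.
- N = 354, mean loading 0.6: 6.8 groups pass, 2.0 of them with alpha 0.4-0.7; KMO 0.85.
- N = 236: about 8 groups at loading 0.6 (KMO 0.77) and about 11 at loading 0.5, where KMO falls below 0.70.
- N = 694: 5.2 to 5.5 groups.
- Parallel analysis returns 5. The surplus is largely absent at a 0.60 loading.

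**4. What the alpha floor admits.** For k items the mean inter-item correlation at a given alpha is r = alpha / (k − alpha(k − 1)).
- k = 3: 0.4/2.2 = 0.18
- k = 5: 0.4/3.4 = 0.12
- k = 10: 0.4/6.4 = 0.06

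At alpha 0.7 the same values are 0.44, 0.32 and 0.19. A true correlation of 0.7 with an error-free criterion would be observed as 0.7 × √0.4 = 0.44.

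The loading rule makes the longer groupings less extreme. Under one factor, items loading 0.40 have r = 0.16. Ten of them give alpha = 1.6/2.44 = 0.66, but four give 0.64/1.48 = 0.43. The floor therefore matters most for small fragments, which is what over-extraction produces.

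**The case against.** The strongest reply is that eigenvalue > 1 is never used alone. Loading thresholds, scree plots, KMO, two independent analysts and agreement across mode and sample stand beside it, and alpha 0.4 is a floor for rejection, not a standard for acceptance. With clean normal items those gates recover the true five groups, the same answer as parallel analysis. In that case the scree also shows a clear break: the fifth and sixth eigenvalues are 4.1 and 1.1 at N = 694, and 4.0 and 1.4 at N = 354. The items were written to a conceptual model and cognitively tested, and 90 is a branching maximum.

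Much of this stands. A reader might infer that chance groupings become scale dimensions, or that comparing structures across samples is comparing noise. The documents do not support that. At N = 354, 694 and 1048 noise groups almost never reach alpha 0.4, and noise KMO is well below 0.70. In the small subgroups (118 and 154) noise groups do pass alpha, but KMO still stops them, and the postpartum structure is compared with the final one instead of defining it.

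The reply does not cover skewed items. Real structure lifts KMO above its limit, and KMO says nothing about the number of factors. The stricter loading is not a free cure either: with ten true factors of mean loading 0.5 at N = 1048, eigenvalue > 1 followed by a 0.60 cut left 8.4 groups. How the criteria combine may be set out in the full plan, and its absence from an article is not counted here.

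**Conclusion.** The point holds in a limited form. Eigenvalue > 1 over-extracts heavily with this many items. The plan's other gates deal with pure chance in the main samples, but not fully with fragments of real dimensions. The expected surplus is about two to three groupings beyond five at N = 354, more in the clinical CASI arm (about 8 to 11, although KMO would stop the weaker-loading case), and about half a grouping at N = 694.

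These counts rest on assumed skew, loadings and simple structure, and on a mechanical use of the numeric gates at the 0.40 loading. Scree reading and agreement across samples could remove some of the surplus. Exact counts move with category spacing and cross-loadings. The 0.44 figure is a bound at the alpha floor, not an expected effect. Severity is minor to moderate.

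**What to change.** Replace eigenvalue > 1 with parallel analysis to set the number of factors. Compare each eigenvalue with those from simulated or permuted data of the same N and number of items, separately for each sample and mode in which a structure is fitted. Permutation keeps each item's skew. Keep the scree plot as support, and the loading, KMO and consistency criteria as they are.

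Report alpha for each retained dimension, and mark those below about 0.7 as low-reliability when the multitrait-multimethod correlations are read. The 0.7 is a convention and open to debate, so it is proposed as a flag and not as a new rejection rule.

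The cost is a few lines of code and a sentence or two of text, with no new data. The downside is slightly more analysis work, and fewer dimensions may be retained.

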## Discussion

### Challenges in validating “health”

Many health care providers have spent their clinical and research careers studying and treating women with urinary symptoms as evidenced by the greater than 50 validated instruments to assess symptoms and quality of life impact in women with LUTS [43]. Previous efforts have focused on defining and treating the disease and not on prevention. The long-term goal of the PLUS Consortium is to decrease the incidence and prevalence of LUTS in women by identifying and then modifying risk and protective factors. Central to this goal is the ability to measure bladder health across a woman’s life course. The PLUS-BHI development and validation described in this manuscript is considered by the PLUS Consortium to be the cornerstone of future efforts in LUTS prevention research.

Critical to the development of the PLUS-BHS for research purposes is having a definition for bladder health [9, 44]. One of the greatest challenges of developing the PLUS-BHS is that we are measuring an abstract theoretical construct such as bladder sensation (a component of bladder health) by asking specific questions that are intended to capture the range of meaning of normal and abnormal “bladder sensation” [45]. We recognize that the questions about bladder function are likely to be interpreted in numerous ways by respondents due to the inability to discriminate between the responses. This is compounded by the reality that the presence of bladder symptoms in women are often considered a “normal” part of aging or secondary to childbirth. As a result, a woman might choose a response that describes her urinary leakage accurately, but attribute minimal disruption in her quality of lifestyle or bother to the symptom because she has been conditioned to believe it is normal. In addition, some LUTS are episodic such as stress incontinence or urinary tract infection symptoms yet are contributors or detractors from bladder health. Additional challenges to measuring overall bladder health relate to the fact that responses to questions can vary based on whether or not a woman is experiencing symptoms at the time of the instrument completion or has ever experienced any symptoms across her life course. Finally, it is challenging to design a measurement of health that is generalizable and interpretable across populations, the life course and settings. To address these issues, we use multiple samples across population and bladder health states and include a clinical interview and review of specific bladder testing by a variety of judges to improve use of the instrument across contexts.

### Strengths and limitations

One of the primary intended uses of the validated PLUS-BHS is to establish a U.S. general population estimate of women’s bladder health, across the life course. To ensure the PLUS-BHS is valid for this inference it is essential to validate using a national general population sample of women. Some of the challenges in conducting national population research is the identification of a representative sample frame, minimizing the well-known problem of coverage error. With survey methods sampling, the DSF with household level enumeration of every known mailing address within the U.S. is the address base sampling frame with the lowest coverage error that exists. The use of random assignment of both general population participants as well as, general clinical participants to the multiple modes (PAPI, CASI and within CASI Web primary as well as push to web) allows a valid and unconfounded comparison of differences in both response rate, item-response as well as distributional differences across mode. The inclusion of clinical samples using community based recruitment allows a clinical evaluation of women across the spectrum of potential bladder health. The inclusion of objective clinical test data provides the “hard ratings” required as a standard of evidence for valid inference with the intended use of the PLUS-BHS. A major strength of our validation work is the inclusion and evaluation of women during the postpartum period. While we would not expect women’s bladder health to be considered stable during pregnancy, we expect the postpartum period to be a factor in women’s bladder health over their lifetime.

While the goal of the PLUS-BHS is to be used across the female lifespan including adolescent girls and adult women, this initial validation was limited to English speaking women ≥ 18 years of age. The development of a similar instrument for adolescents and Spanish speaking females is underway and will be facilitated by the outcomes of the VIEW study. Since the instrument is specifically designed for women, who have different lower urinary tract anatomy and symptoms when compared to men or transgender women, this instrument is not intended for use with males or adolescent females. Lastly, the PLUS-BHI is only tested for clinical research in ambulatory women; thus, women who have functional and neurogenic LUTS are not included in the spectrum of bladder health assessed by the PLUS-BHI. The questions and answer stems might not be appropriate in this population and would need further testing to determine their ability to discriminate bladder health from bladder disease in certain populations.

The VIEW study includes women from the general population and from those recruited around clinical centers, those who are recently postpartum and who attend clinical practices for health care. While this range of recruitment can be a strength of the study to assure a wide range of contexts, it is also possible that the distribution of bladder health may not be comparable between the populations. While clinical center recruitment was intentionally designed in order to capture the full spectrum of very healthy to very unhealthy, the screening instrument we used (the PPBC) may not accurately discriminate across the true severity of disease and does not address impact of symptoms. Similarly, validated questionnaires were not used to stratify women according to type of LUTS for inclusion in the clinical examination. It is also possible that women recruited from clinical practices, specifically specialty practices (e.g. urology, urogynecology) and with self-reported severe symptoms may be fundamentally different than women who may have symptoms but who do not seek out care for LUTS. As a result, the PLUS-BHS may discriminate between participants with similar LUTS who have different expectations for their bladder health. Modifications to the scoring of the PLUS-BHS may need to be made for general, clinical and postpartum populations and the PLUS-BHS would not be as generalizable as desired.

The VIEW study participants are randomized to the use of paper or computer instruments in order to evaluate potential mode effect on items and subsequently develop a scale that is mode agnostic. While we aim to have a mode agnostic instrument, we acknowledge that it may not be feasible to conduct population based research using CASI mode given systemic biases associated with women’s access to technology. Additionally, while the use of smartphones and technology has increased in many parts of the U.S., we anticipate differences in response rates by mode of administration across age groups and by socioeconomic status.

In conclusion, we present the rationale and approach to development and validation of a novel instrument for the measurement of bladder health in epidemiologic research. The scored bladder health scale will provide the foundation to assess the distribution of bladder health in women and girls within the United States and allow for future study of a variety of factors associated with bladder health. With this foundational instrument developed, future iterations and adaptations will be possible to include adolescent and Spanish-speaking females and pregnant populations. Additional efforts in the future will focus on assessing sensitivity to change and minimum important differences for use in intervention studies. These data will inform future intervention trials in the promotion of bladder health and prevention of lower urinary tract symptoms in women across the life course.

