### Study administration

#### General population

The study flow for the general population cohort is outlined in Fig. 1. All households in the DSF sample frame are mailed a pre-notification letter including a $2.00 bill and a tri-fold color brochure describing the study, with a request for participation by the female in the household, age 18 or over with the most recent birthday. Households are randomized 1:2 to PAPI or CASI. The imbalanced randomization reflects an expected lower response rate from CASI [23]. For those randomized to PAPI, the first PLUS-BHI packet mailing includes $10 as incentive and a stamped envelope addressed to the Scientific and Data Coordinating Center (SDCC). Non-respondents are sent replacement packets up to 4 times. Those randomized to CASI are asked to provide a valid email address using the provided postage paid return envelope. Respondents who do not provide an email are necessarily assigned to the push-to-web group, wherein future paper mailings include an electronic link for online survey completion. Households who do provide an email address are randomized to either the push-to-web group or to receive an email with a link to the survey (referred to as the web primary group). This second randomization allows a full comparison of respondents who fully elect to respond via electronic mode to those who do not. Those in the web primary group are additionally randomized 1:1 to receive $5 thank you for providing an e-mail address. A total of four follow-up packets are mailed to non-respondent households wherein the final contact includes a paper version of the survey.

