#### Clinical center populations

The study flow for the general population cohort is outlined in Fig. 2. Once eligibility criteria are established (Table 1), verbal consent is obtained; and participants are enrolled and randomized to PAPI vs. CASI mode 1:2 in blocks of 3, stratified by center. Those who do not have email capability are offered participation in the PAPI arm. Those assigned to PAPI mode are mailed the same survey packet described for the general population. Those participants assigned to the CASI version are emailed a unique link to complete the surveys and PLUS-BHI validation material online, which are captured directly via REDCap [27]. Non-respondents are mailed or emailed replacement packets up to three times every 15 days.

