**Fig. 2 Fig2:**
[figure not shown]
Clinical center sample study flow. BH, Bladder Health; BHI, Bladder Health Instrument; CASI, Computer Assisted Self Interview; PAPI, Paper and Pencil self-Interview; RA, Random Assignment. *Note*: Postpartum sample N = 154 and are not randomized to BHI mode of administration

Participants who complete the initial materials are contacted and scheduled for an in-person clinical evaluation. Upon scheduling they are mailed a decorative box containing a copy of the written consent form, the 2-day bladder symptom diary (Additional file 1), a 1-day frequency-volume bladder dairy (Additional file 2), a voiding hat to measure urine volumes, and detailed instructions for completion of all material. Participants are contacted at least 4 days prior to the clinical evaluation to ensure completion of diaries prior to the visit.

On the day of the in-person evaluation, participants proceed with written informed consent, and bladder diaries are reviewed to confirm completion. Participants undergo an interview with a bladder health judge followed by clinical testing procedures to obtain the objective measures of bladder function outlined below. Participants receive prorated compensation up to $100 for completion of the study.

Women recruited for the postpartum population are allowed to select their preferred mode of administration rather than be randomized given the additional demands of completing study procedures for new mothers. The survey packet is sent to be completed within the 6–12 weeks postpartum window. Otherwise the steps are identical to the general clinical center population with respect to the judge assessments and in-person clinical evaluation conducted.

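### Random assignment protects the mode comparison of response rates, but not, as the article claims, the comparison of item answers and their distributions

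*Protocol article*

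**What the plan says.** The claim stands in the Protocol article under Strengths and limitations. Random assignment of the general population and general clinical participants to paper, computer and the two web variants is said to allow a comparison that "allows a valid and unconfounded comparison of differences in both response rate, item-response as well as distributional differences across mode".

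The procedures are described under Study administration:

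- **General population.** "Households are randomized 1:2 to PAPI or CASI", and "The imbalanced randomization reflects an expected lower response rate from CASI". Within CASI, "Respondents who do not provide an email are necessarily assigned to the push-to-web group"; only households that give an email are randomised between push-to-web and web primary. CASI non-respondents receive follow-up mailings "wherein the final contact includes a paper version of the survey".
- **Clinical center sample.** Women are randomised 1:2 in blocks of 3, stratified by center. However, "Those who do not have email capability are offered participation in the PAPI arm".
- **Postpartum sample.** These women are "allowed to select their preferred mode of administration rather than be randomized".

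Under Strengths and limitations the authors add that "we anticipate differences in response rates by mode of administration across age groups and by socioeconomic status".

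The Analysis plan compares responses between PAPI and CASI in the general and clinical samples separately, using Tukey's HSD or chi-square (Fisher's test where needed). Items that differ significantly by mode are considered for removal. The section mentions no adjustment and does not say whether mode means assigned or completed mode.

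**The concern.** A mode-agnostic scale is one of the article's two stated methodological aims, and the mode test is one of the filters that decide which items reach it. If the PAPI and CASI respondents differ in age, socioeconomic position or access to technology, and these relate to bladder health, an unadjusted test cannot separate the effect of the medium from the effect of who answered in it. The error can go either way: a sound item may be flagged because different women answered it, or a real mode effect may be hidden by an opposing difference in composition. A claim of freedom from confounding also tells the analyst and the later reader that no such check is needed.

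**Working it through.** **The plan's own figure.** The only sample-size figure is participants per item: 694/90 = 7.7 (stated as 8) and (694 + 354)/90 = 11.6 (stated as up to 12). Both reproduce, but they concern factor analysis. The article gives no power, effect size, SD, email rate or response rate for the mode comparison, so the sizes below are illustrations.

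**Which outcomes randomisation protects**

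1. *Response rate, general sample.* Households are assigned before anyone responds, and every assigned household counts in the denominator. The comparison by assigned PAPI or CASI is unconfounded.
2. *Item answers and distributions, general sample.* These are seen only in respondents. The target yield is 694/6000 = 11.6%. If the 1:2 split of 2000 and 4000 households were meant to give equal completes (assumption), response would be 347/2000 = 17.4% on PAPI and 347/4000 = 8.7% on CASI. Two small fractions of unequal size, expected by the authors to differ by age and socioeconomic status, are not exchangeable merely because their households were randomised.
3. *Item answers, clinical sample.* Women without email are found only among those who answer on paper.

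**Clinical illustration.** Let f be the share of the 354 women without email, all on PAPI, with the rest split 1:2.

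- PAPI size = 354 × [f + (1 − f)/3]; CASI size = 354 minus PAPI size.
- Share of PAPI without email: s = f / [f + (1 − f)/3].
- Spurious difference in SD units: b = s × d, where d is how far women without email differ on the item.
- SE = √(1/PAPI + 1/CASI).
- Chance of a flag at two-sided 5% with no true mode effect: P(|Z + b/SE| > 1.96).

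| f | PAPI / CASI | s | SE | b, d = 0.2 | flag | b, d = 0.5 | flag |
|---|---|---|---|---|---|---|---|
| 5% | 130 / 224 | 13.6% | 0.110 | 0.027 | 6% | 0.068 | 9% |
| 10% | 142 / 212 | 25.0% | 0.109 | 0.050 | 7% | 0.125 | 21% |
| 15% | 153 / 201 | 34.6% | 0.107 | 0.069 | 10% | 0.173 | 36% |

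For f = 10%: s = 0.10/(0.10 + 0.30) = 0.25; with d = 0.5, b = 0.125; b/SE = 0.125/0.109 = 1.15; flag probability 0.21.

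**General-sample illustration.** Assume that a group making up a share g of PAPI respondents responds to CASI at a fraction r of the others' relative rate. Its share of CASI respondents is gr/(gr + 1 − g), and b = [g − gr/(gr + 1 − g)] × d. With 347 completes per mode, SE = √(2/347) = 0.076.

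- g = 0.3, r = 0.75, d = 0.2: b = (0.300 − 0.243) × 0.2 = 0.011, flag about 5%.
- g = 0.4, r = 0.5, d = 0.5: b = (0.400 − 0.250) × 0.5 = 0.075, flag about 17%.
- g = 0.4, r = 0.25, d = 0.5: b = (0.400 − 0.143) × 0.5 = 0.129, flag about 40%.

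The effect runs from negligible to large, depending on inputs that the article does not give.

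**The case against.** Most of the defence has some force.

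- *Allocation really is random.* A reader might infer that email access and choice determine who is in each mode. The documents do not support that. Households and clinical women are randomised first, and the other factors only modify the result.
- *Clinical women without email may have been randomised first and then offered paper.* The text does not settle the order. If so, they are crossovers, and a comparison by assignment is not biased by their move. Either way they answer only on paper, so a comparison by mode used mixes them into PAPI alone.
- *Analysis by completed mode is not stated.* It would be tempting to say that late CASI responders are moved into the paper group. The article does not say so, and the choice may be left to the analysis plan.
- *Web primary versus push-to-web.* The claim names this contrast, and it is valid among email providers. Nothing says that non-providers will be pooled into it, and item removal rests on PAPI versus CASI.
- *Postpartum women.* Their free choice of mode is disclosed, and the claim names only general population and general clinical participants. The plan's reference to the clinical samples leaves open whether they enter the mode contrast; that is an ambiguity and not an error.
- *Removal is not automatic.* Flagged items are only considered for removal, so a false flag need not cost an item.
- *Access bias is admitted.* The limitations name it and expect differential response, but they do not withdraw or qualify the claim for item answers and distributions.

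What remains is an affirmative claim, about two of its three outcomes, that the article's own procedures and expectations do not bear out.

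**Conclusion.** The concern holds in limited form. The word unconfounded is right for response rate by assigned PAPI or CASI among randomised households, and wrong for item answers and distributional differences. For the clinical sample, with 5–15% of women without email and a difference of 0.2–0.5 SD (both assumed), the spurious mode difference is about 0.03–0.17 SD and the false-flag probability about 6–36% against a nominal 5%. At the low end the problem is trivial; at the high end the item filter is unreliable. The structural point does not depend on these values. The claim and the mode analysis should be corrected before items are removed. The design is not invalid, because the randomisation is sound and the remedy lies in the analysis.

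**What to change.** 1. Limit the unconfounded claim to response rate by assigned mode.
2. Flag clinical women without email; keep them in the study and in the factor analyses, but out of the mode contrast.
3. Compare items by assigned mode: in the clinical sample adjusted for center; in the general sample weighted or adjusted for age, education and sampling stratum (assuming education is among the demographic items, which the article does not list). Report completed mode as a sensitivity analysis.
4. Restrict any web-primary versus push-to-web contrast to email providers randomised between the two.
5. If postpartum data would otherwise enter the mode contrast, leave them out, because these women chose their mode.

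**Cost.** Mainly analysis wording and one flag per clinical participant; no new recruitment. The clinical comparison becomes slightly smaller: at 10% without email, about 35 of 354 women leave it. Analysis by assigned mode dilutes a true mode effect where CASI households answer on paper; if 10–40% of CASI-assigned completes were on paper (assumption), 90–60% of the effect would remain, which is why completed mode is worth showing beside it. Adjustment cannot remove nonresponse bias from unmeasured differences, so the narrower claim is needed even with adjustment.
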